### Outcome measures

All outcome measures are assessed at baseline and again at 6 months.

#### Sample characteristics

To describe the sociodemographic characteristics of participants, all surveys include demographic information (e.g., biological sex, age, race/ethnicity, nativity). In addition, a clinical description of the sample will be provided using the 10-item Center for Epidemiological Studies-Depression (CES-D) scale for depressive symptoms [35], the Perceived Stress Scale (PSS) [36] and perceived availability of social support using the Interpersonal Support Evaluation List (ISEL) [37]. *Timely access to services* is measured using dates of substance abuse screenings, trauma assessments and treatment service provision recorded in the Needs Portal.

*Child safety and permanency* outcomes are operationalized as (1) the number of days in out-of-home care, (2) whether the family re-unifies in out of home care and (3) the number of new child welfare referrals occurring after the initial referral that led to program participation using administrative child welfare data from the statewide automated child welfare information system (SACWIS).

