## Methods / design

The overall goals and objectives of the intervention are:
Increase timely access to services among substances abusing parents involved in the child welfare system in Fairfield and Pickaway counties1.1 Develop procedures to coordinate services between the child welfare system, substance abuse and behavioral health providers, and juvenile/family court in a specified single MOU.1. 2 Conduct substance abuse and trauma-exposure screening and assessment within 30 days of entering the child welfare system.1. 3 Reduce the wait time between referral to services and initiation of substance use and behavioral health services.Enhance child safety and improve permanency2.1 Reduce length of stay in out-of-home placement for children in EPIC program compared to substance-affected families not receiving EPIC.2. 2 Increase rates of reunification among families involved in EPIC compared to substance-affected families not receiving EPIC.2. 3 Reduce recidivism for child welfare investigations and re-entries into foster care among parents receiving EPIC compared to substance-affected families not receiving EPIC.2.4 Identify which intervention components implemented via EPIC were more likely to increase positive outcomes for families.Increase child, parent, and caregiver well-being3.1 Decrease substance use/abuse addiction severity among parents and the percentage of parents completing substance abuse treatment who maintained abstinence post-treatment.3. 2 Reduce trauma symptoms experienced by children.3. 3 Increase resilience and attachment in children.3.4 Increase knowledge about trauma-exposure among kinship caregivers.3.5 Improve parenting among kinship caregivers.

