#### FTDC with MOUD

FTDC is considered the most effective intervention to improve substance abuse treatment initiation and completion in child welfare populations [21]. Parents who participate in FTDC are more likely to enter substance use treatment, get into treatment quicker, stay in treatment longer, and complete treatment more often [22–24]. Additionally, families who complete FTDC are more likely to be reunified with their children as compared to parents who do not participate [22–25]. To bolster the effects of FTDC, EPIC participants also have access to MOUD, which has been shown to reduce withdrawal symptoms, lower the risk of relapse, address cravings, and provide medical supervision for individuals struggling with addiction [26]. Further, MOUD is associated with an increased likelihood that children will remain in their parents’ custody [27].

*Peer recovery supporters*—also called “recovery coaches”— are advocates for parents and their primary focus is to help get parents into treatment and support them so that they stay there. Peer recovery supporters are certified by the Ohio Department of Mental Health and Addiction Services [28] and must complete 40 h of in-person training, 16 h of online training, and pass a test. They are individuals who formerly had substance use issues, but have been clean and sober for at least 3 years. Peer recovery supporters provide comprehensive clinical assessments, service planning, referral, advocacy, case management, and outreach services. Peer recovery supporters have had great success in reducing substance use and improving child welfare outcomes. Peer recovery supporters improve access to substance use treatment, decrease time children spend in out-of-home care, increase the odds of reunification, decrease maltreatment recidivism, and reduce racial disparities in reunification [29–31]. Under EPIC, peer recovery supporters are trained and supervised by two partner behavioral health agencies, Ohio Guidestone and Integrated Services. Peer recovery supporters make individual or joint home visits with child welfare caseworkers and are otherwise available via phone and text as needed. They also attend multi-disciplinary child welfare team meetings to provide expert consultation on cases.

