### Participant recruitment, eligibility and group assignment

Participants are recruited from Fairfield and Pickaway County Children Services. The overall case flow is provided in Fig. 1. Within 7 days of the initial child welfare investigation, parents complete the UNCOPE assessment, a universal screening tool for substance use administered to all parents entering the child welfare system [33]. Parents who score a 3 or higher on the UNCOPE, are considered eligible for EPIC and receive a drug screen. Eligible parents are alternated into EPIC, OhioSTART or treatment as usual (TAU). Ultimately, assignment to EPIC is determined based on caseload, but is typically offered to every third case in Fairfield county and every other case in Pickaway county. Parents who consent to EPIC are connected to peer recovery supporters who mentor parents through the process. Parents are also referred to FTDC with the option to receive MOUD, and lastly when children are placed at home with parents or with kinship caregivers, relational skill building services that include financial assistance for child care, respite and transportation services. EPIC participants receive substance abuse and behavioral health treatment services through local providers including from two partner agencies: Integrated Services for Behavioral Health and Ohio Guidestone.

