### Statistical plan

Baseline descriptive statistics including sociodemographic characteristics, addiction severity and child welfare allegations will be provided for EPIC participants and comparison groups. For continues variables, means and SDs will be provided and for categorical variables, counts and percentages are provided.

Due to the likelihood of censored measures when families are still involved in the child welfare system, survival analysis will be utilized to assess program effects on length of stay in out of home care. Logistic regressions will be used to estimate the relationship between activities and family was reunification, subsequent child maltreatment investigations, and subsequent child maltreatment substantiations. A series of linear regressions will be used to estimate the relationship between our outcome measures and various independent variables (e.g., age, biological sex). Additionally, a paired samples t-test will be conducted to examine the changes in mean scores in child, parent and caregiver well-being outcomes (e.g. ASI or CBCL) between baseline and 6-months follow-up.

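### First removal after entry is not an outcome, and length of stay read as time to exit compares only placed children, so prevented removals can go unseen and bias can run either way

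*Protocol article*

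**What the plan says.** All places are in the protocol article.

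- **Objectives (Methods / design).** Objective 2.1 is "Reduce length of stay in out-of-home placement for children in EPIC program", relative to substance-affected families without EPIC. Objectives 2.2 and 2.3 concern reunification, repeat investigations and foster care re-entry.
- **Outcomes (Sample characteristics).** The safety and permanency outcomes, taken from SACWIS, are "the number of days in out-of-home care", "whether the family re-unifies in out of home care" and "the number of new child welfare referrals occurring after the initial referral that led to program participation".
- **Analysis (Statistical plan).** The article states that "survival analysis will be utilized to assess program effects on length of stay in out of home care". The reason given for choosing this method reads "Due to the likelihood of censored measures when families are still involved in the child welfare system". Logistic models cover reunification and later investigations and substantiations.
- **Entry (Participant recruitment, eligibility and group assignment).** Parents are screened within 7 days of the first investigation. The Fig. 1 legend says a substantiated report instead. Neither is a removal. Parenting support is offered "when children are placed at home with parents or with kinship caregivers".
- **Rationale (FTDC with MOUD).** The text cites evidence that "MOUD is associated with an increased likelihood that children will remain in their" parents' custody.
- **Power analysis.** The survival analysis is given N = 750, the full sample.

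**The concern.** A family can enter EPIC with the child at home, and the child may or may not be removed later. That first removal is recorded by no objective or outcome. Reunification and re-entry both presuppose an earlier removal. A removal on a case that is already open need not produce a new referral.

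The survival analysis is justified by open cases being censored, so its natural event is exit from care. A child who is never placed has no time at risk of exit. For children at home at entry, the analysis would then compare those later placed under EPIC with those later placed elsewhere. These groups are formed after entry, by an event that EPIC may change. Matching at entry does not repair this, and neither does a larger sample. The reunification model has a related difficulty: never-removed families are either dropped or, if coded as not reunified, counted as failures.

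At stake is objective 2.1. A reader could not tell an effect on length of stay from a change in who is removed.

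**Working it through.** **The plan's own figure.** The only related figure is the survival power of 1.00 at N = 750, effect size 0.2, alpha 0.05. Whether it reproduces depends on what 0.2 means. With 750 events, a log hazard ratio of 0.2 gives 0.73-0.78 two-sided, while a hazard ratio of 0.2, or f = 0.2, gives 1.00. The metric is in Additional file 1, which is not shown, so this figure is not called wrong and the point does not rest on it.

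**Does any listed item record first removal?**

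| Item | Needs an earlier removal? | Records first removal? |
|---|---|---|
| Days in out-of-home care | Value for a never-removed child not stated | Only if 0 days is counted |
| Reunification | Yes | No |
| Re-entry into foster care | Yes | No |
| New referrals, investigations, substantiations | No | No |

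**Hand illustration (all inputs assumed).** Take 100 families with the child at home at entry. The comparison group has 30 removals: 15 mild (6 months) and 15 severe (15 months). EPIC changes no individual stay; it only prevents some removals.

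Mean stay = (6 × mild + 15 × severe) / (mild + severe). Months in care per family = (6 × mild + 15 × severe) / 100.

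Comparison group: (90 + 225)/30 = 10.5 months; 315/100 = 3.15 months per family.

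| Type prevented | Share prevented | Mild, severe left | Mean stay (months) | Months per family |
|---|---|---|---|---|
| Mild only | 20% | 9, 15 | 279/24 = 11.6 | 2.79 |
| Mild only | 33% | 5.1, 15 | 255.6/20.1 = 12.7 | 2.56 |
| Mild only | 50% | 0, 15 | 225/15 = 15.0 | 2.25 |
| Random | 20% | 12, 12 | 252/24 = 10.5 | 2.52 |
| Random | 33% | 10.05, 10.05 | 211.05/20.1 = 10.5 | 2.11 |
| Random | 50% | 7.5, 7.5 | 157.5/15 = 10.5 | 1.58 |
| Severe only | 20% | 15, 9 | 225/24 = 9.4 | 2.25 |
| Severe only | 33% | 15, 5.1 | 166.5/20.1 = 8.3 | 1.67 |
| Severe only | 50% | 15, 0 | 90/15 = 6.0 | 0.90 |

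The rise from 10.5 to 15.0 months belongs to the mild-only scenario alone. Months in care per family fall in every row.

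**Simulation.** Removal and stay share a severity factor; 400,000 families per scenario, one-year horizon, no true effect of EPIC on stay. Example: 50% removed under comparison, EPIC prevents 40% of removals, so 0.50 × 0.60 = 30% are removed under EPIC.

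| Type prevented | Exit-rate ratio, removed children | Mean days, removed children | Mean days, all families (0 if never removed) |
|---|---|---|---|
| Mild | 0.78 | 210 to 236 | 105 to 71 |
| Random | 1.00 | 210 to 210 | 105 to 63 |
| Severe | 1.16 | 210 to 195 | 105 to 59 |

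Over the assumed ranges (30-70% removed, 20-40% prevented) the ratio is 0.77-0.92, 1.00 and 1.05-1.19 respectively. A ratio below 1 means slower exit under EPIC.

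**The case against.** **The risk set is not stated.** The article gives neither a time origin nor a risk set. A count of days can be 0, and N = 750 fits a count over all families. On that reading prevented removals are credited. This stands as a possibility, so it cannot be said that they certainly earn no credit. But the text never gives never-removed children 0 days, and the reading sits badly with a method chosen because open cases are censored.

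**Such detail belongs in a fuller plan.** This is fair for time origin and coding, and their absence is not the point. The objectives and outcome list are set in this article, and removal is in neither. The method named for objective 2.1, on its natural reading, selects on an event after entry.

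**The direction is unknown.** A reader might infer that EPIC will be left with the harder cases and will look harmful. The documents do not support that, because nothing says which removals EPIC would prevent.

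**The size is unknown.** The share of children at home at entry is not given, and the phrase on home placement also covers kinship caregivers. If most placements precede enrolment, the distortion is small. Outcomes are said to be assessed at 6 months. Taken literally, that would censor the 15-month stays in the illustration, so its mean differences would not be seen as such.

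**The stakes are limited.** The abstract lists length of placement among additional outcomes, not primary ones. Referrals, investigations and substantiations do not require a removal and could still show a gain. The MOUD sentence reports literature and sets no trial objective, so nothing is contradicted. All of this stands.

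**Conclusion.** The point holds in a limited form. Entry is not conditional on removal, some children are at home, and first removal after entry is not an outcome. The length-of-stay survival analysis, read as time to exit, compares a group whose make-up EPIC may change. It can therefore miss prevented removals and be biased against EPIC (mild removals prevented), not at all (random prevention) or in its favour (severe removals prevented). The simulated exit-rate ratios run from 0.77 to 1.19 with no true effect on stay. Those figures rest on assumed removal and prevention shares and apply to children at home at entry.

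The documents do not show that prevented removals earn no credit anywhere, or that the trial would report harm. Length of stay is an additional outcome serving objective 2.1. The change is worth making because days in care over all families fell in every scenario examined, whichever removals were prevented.

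**What to change.** In the outcome list and Statistical plan, using SACWIS:

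1. For all families, compare days in out-of-home care within one fixed window from enrolment (or the matched index date for comparison families), counting 0 for children never removed.
2. For children at home at entry, report time from that date to first removal.
3. Restrict the length-of-stay survival analysis to children already in care at entry, whose placement EPIC could not have influenced.

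The cost is wording, one more reported outcome and a smaller length-of-stay subset. SACWIS already supplies days in care, so no new data source is needed. The smaller subset costs power. As an illustration, take a log hazard ratio of 0.2, EPIC against the rest (one third against two thirds), two-sided 5%, with every stay ending. Power = Φ(0.2 × √(stays × 1/3 × 2/3) − 1.96), which gives 0.73 with 750 stays, 0.45 with 375 (50% of families) and 0.29 with 225 (30%). The shares are assumptions. The all-family comparison keeps the full 750.

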#### Parent and child well-being outcomes

Addiction severity is measured using the drug and alcohol use items in the Addiction Severity Index-Self Report (ASI-SR) [38]. Trauma symptoms in children are measured using the Children’s Trauma Assessment Center (CTAC) trauma screening checklist [39]. The CTAC—separately for children ages 0–5 and 6–18)—can be administered by clinicians and child welfare caseworkers in evaluating children for exposure to trauma and trauma-related symptoms. The effect of sensory processing on functional performance among children 0–6 months and 7–17 months is measured using version 1 and 2 respectively of the Infant Toddler Sensory Profile (ITSP) [40], behavioral and emotional problems in younger children (18 months to 5 years) and in school age children and adolescents (6 to 18 years) are measured using the Child Behavior Checklist (CBCL) [41] and parenting skills is measured using the 40-item Adult Adolescent Parenting Inventory, version 2 (AAPI-2) [42]. The AAPI-2 breaks down into five parenting behavior subscales: expectations of children, parental empathy towards children’s needs, use of corporal punishment, parent-child family roles, and children’s power and independence. Lastly, resiliency and attachment are measured using the Protective Factors Survey [43].

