**Methods:**

EPIC is a quasi-experimental study. Under the program**,** child welfare-involved adults who screen positive for substances are matched with a peer recovery supporter. Participants are also incentivized to participate in family treatment drug court, medications for opioid use disorders and home-based parenting supports. Participating adults (*N* = 250) are matched with comparison groups from counties participating in a separate intervention (Ohio START) and to those receiving treatment as usual, resulting in a final sample of 750 adults. Primary outcomes including addiction severity, child trauma symptoms, resilience, and attachment are assessed at baseline and at program completion. Additional outcomes include timely access to treatment services, length of placement in out-of-home care and recidivism into the child welfare system.

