#### Power analysis

We performed a series of power analyses using G*Power [44] and for each analytic method. Assuming a small effect size of 0. 2, we will be able to reject the null hypothesis with probability (power) of 1.00 (survival analysis, *N* = 750), 0.81 (logistic regression, *N* = 750), 0.88 (paird t-tests; *N* = 250) and 0.99 (linear regression, *N* = 250). The Type I error probability associated with these tests is 0.05. A detailed report is presented in Additional file 1.

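### The single paired t-test power of 0.88 at N = 250 cannot hold for both the ITSP and the CBCL, which divide at most 250 focal children by age

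*Protocol article*

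**What the plan says.** In the Protocol article, the section on parent and child well-being outcomes assigns child instruments by age. Sensory processing "among children 0–6 months and 7–17 months is measured using version 1 and 2 respectively of the Infant Toddler Sensory Profile" (ITSP). Behavioral and emotional problems "in younger children (18 months to 5 years) and in school age children and adolescents (6 to 18 years") are measured with the CBCL. The CTAC trauma checklist also has separate forms, for ages 0–5 and 6–18. The ASI-SR, the AAPI-2 and the Protective Factors Survey are given no child age bands.

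The section on data sources says that each parent answers for one focal child only.

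Under Statistical plan, "a paired samples t-test will be conducted to examine the changes in mean scores in child, parent and caregiver well-being outcomes", with the ASI and the CBCL as examples and 6 months as the follow-up point.

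Under Power analysis, one figure serves this test. The assumptions are "Assuming a small effect size of 0. 2" and "The Type I error probability associated with these tests is 0.05", and the result is "0.88 (paird t-tests", at N = 250.

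On timing, the outcome section says "All outcome measures are assessed at baseline and again at 6 months". The data-sources section instead puts the second survey between 6 and 12 months after the program ends, and the Abstract puts the second assessment at program completion.

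**The concern.** A paired t-test has as many pairs as there are people with a score on the same scale at both waves. The ITSP stops where the CBCL starts, and each family contributes one child, so every child counted for one instrument at baseline is lost to the other. A power computed for 250 pairs therefore cannot describe both, and the CBCL is one of only two outcomes named for the test.

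A second loss comes on top. Children age between waves, and some move to another form. The article does not say how they enter a change score. The ITSP bands are so narrow that this affects most infants even at 6 months.

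At stake is how a null result in a child outcome will be read. Someone who believes the test had 0.88 power will take a null as evidence against a small change, when the number of usable pairs may have been far too small to show one.

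**Working it through.** **Inputs from the article.** Two-sided alpha 0.05 (the number of sides is not stated; two-sided reproduces the stated power). Effect size 0.2, read as the standardised mean change. 250 EPIC families, one focal child each. Age bands as above, read in completed months: ITSP version 1 from 0 to under 7, version 2 from 7 to under 18, younger CBCL from 18 to under 72, younger CTAC from 0 to under 72.

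**Assumptions.** The article gives no age distribution. I take an infant share (under 18 months) of 10% to 40% and ages spread evenly within each band. No attrition.

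**1. The stated figure.** Power = P(|T| > t(0.975, n − 1)), with T noncentral t on n − 1 degrees of freedom and noncentrality 0.2√n. At n = 250 the noncentrality is 0.2 × 15.81 = 3.16 and power is 0.883. One-sided it would be 0.934. The stated 0.88 is correct for 250 complete pairs.

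**2. How much room the split leaves.** Rounding to 0.88 needs at least 244 pairs, and 80% power needs 199.
- For the CBCL to keep 0.88, at most 250 − 244 = 6 focal children (2.4%) may be infants.
- For the CBCL to keep 80%, at most 250 − 199 = 51 (20.4%) may be infants.
- For the ITSP to reach 80%, at least 199/250 = 79.6% must be infants.

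**3. Power by infant share.** CBCL counts pool its two forms. ITSP counts first take all infants, which is an upper bound, and then only those who keep the same version at 6 months (one third, from step 4).

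| Infant share | CBCL n | Power | ITSP n, all infants | Power | ITSP n, same version | Power |
|---|---|---|---|---|---|---|
| 10% | 225 | 0.85 | 25 | 0.16 | about 8 | 0.08 |
| 20% | 200 | 0.80 | 50 | 0.28 | about 17 | 0.12 |
| 30% | 175 | 0.75 | 75 | 0.40 | 25 | 0.16 |
| 40% | 150 | 0.68 | 100 | 0.51 | about 33 | 0.20 |

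The same-version column still adds the two ITSP versions together. Tested separately, each has fewer pairs.

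**4. Share changing form.** With even ages, the share leaving a band is the gap divided by the band width.
- ITSP version 1 at 6 months: 6/7 = 86%.
- ITSP version 2 at 6 months: 6/11 = 55%.
- All infants at 6 months: (6 + 6)/18 = 67%, so 33% keep their version.
- Younger CBCL to older form at 6 months: 6/54 = 11%.
- Younger CTAC to older form at 6 months: 6/72 = 8%.
- All infants at 9 months: 16/18 = 89%.
- All infants at 12 months: 100%, whatever the age distribution, because the ITSP bands are only 7 and 11 months wide.

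The gap matters because a survey 6 to 12 months after the program ends falls more than 6 months after enrollment. The article gives no program length, so a 12-month gap is a possibility and not a stated schedule.

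**The case against.** The strongest reply is that the article gives power per analytic method and not per instrument, that 0.88 is computed correctly, and that it refers to an additional file with a fuller power report. That file and any analysis plan are not shown, and the handling of children who change form normally belongs there. This stands as far as handling goes: its absence from an article is no error. It does not rescue the figure, because no later document can create 250 pairs for both the ITSP and the CBCL from at most 250 focal children.

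Three stronger readings are tempting and are not supported:
- **That the plan subtracts scores from different instruments.** The article never says so. The test may be meant for same-form pairs only, and the ITSP is covered only through the general reference to child outcomes.
- **That no paired test reaches 250.** The ASI-SR (the other named example), the AAPI-2 and the Protective Factors Survey have no child age bands and can reach 250 before attrition.
- **That the CTAC, which measures a primary outcome, is short of 250.** Its two forms together cover all ages. Clinicians or caseworkers can administer it, and trauma screening is recorded in the Needs Portal, so the one-child limit of the parent survey may not apply. Whether its two forms share a scale is not settled either way.

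It is also fair to say that the severe figures concern the ITSP, which is not listed among the primary outcomes in the Abstract and matches no stated objective. For the CBCL and the CTAC, switching at 6 months is modest.

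**Conclusion.** The point holds in a limited form. The 0.88 is right for 250 pairs and can stand for parent outcomes without age bands, before attrition. It cannot stand for both the ITSP and the CBCL, and that conclusion needs no assumption about ages.

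The size does need one. For infant shares of 10% to 40%, CBCL power runs from 0.85 to 0.68 with its forms pooled; if the forms cannot be pooled, it is lower. ITSP power is at most 0.16 to 0.51, and about 0.08 to 0.20 on same-version pairs at 6 months. With few infants the CBCL loss is small. The ITSP cannot support a paired test at effect size 0.2 anywhere in this range, and it has no same-version pairs at all if the gap from baseline reaches 12 months.

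**What to change.** 1. Replace the single 0.88 with a paired-test power for each instrument, based on the expected number of same-form pairs. Baseline ages of children already enrolled would supply that number without assumptions.
2. Limit paired change scores to children with the same form at both waves, or use age-standardised scores where the instrument has them, and report how many children change form.
3. Report the ITSP descriptively, without a paired test.
4. Reconcile the follow-up timing: 6 months in the outcome section and the Statistical plan, 6 to 12 months after the program ends in the data-sources section, and program completion in the Abstract. The number of same-form pairs depends on which applies.

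A regression of follow-up score on study group is not proposed here, because the article describes the surveys as EPIC family surveys and does not establish that comparison families complete them.

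The cost is a change of wording and a less favourable power statement for the child outcomes. No new data are needed.
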